## Abstract

**Background:**

Odontectomy is a common surgical procedure often associated with significant preoperative anxiety, particularly when performed under general anesthesia. Anxiety can lead to physiological changes, such as increased blood pressure and heart rate, and may affect anesthetic requirements and postoperative recovery. Virtual reality (VR) has emerged as a promising non-pharmacological intervention to reduce anxiety through immersive distraction.

**Objective:**

This study aims to evaluate the effectiveness of VR in reducing preoperative anxiety in patients undergoing odontectomy under general anesthesia. The study will assess anxiety using both subjective measures (Amsterdam Preoperative Anxiety and Information Scale, APAIS) and objective biomarkers (salivary alpha-amylase, salivary cortisol, and vital signs).

**Methods:**

This is a prospective, randomized controlled trial. Patients aged 17‐40 years undergoing odontectomy under general anesthesia at the Dental and Oral Hospital, Universitas Padjadjaran, will be recruited. Participants (n=32) will be randomly assigned to either the intervention group (VR experience of the operating room) or the control group (standard verbal education). Data collection includes salivary samples (alpha-amylase and cortisol), vital signs (blood pressure, heart rate, respiratory rate), and APAIS scores measured at baseline, immediately post-intervention, and 15 minutes post-intervention. Data will be analyzed using independent and paired *t* tests or Mann-Whitney and Wilcoxon tests, depending on normality.

**Results:**

The study is scheduled to be conducted between October 2026 and December 2026. The findings will provide evidence regarding the efficacy of VR as a standard anxiolytic tool in oral surgery.

**Conclusions:**

If effective, VR could serve as a non-invasive, safe alternative to pharmacological premedication for managing preoperative anxiety, potentially improving surgical outcomes and patient comfort.

## Introduction

Odontectomy, the surgical removal of impacted third molars, is one of the most frequent procedures in oral and maxillofacial surgery [1,2]. Due to the complexity of the procedure and the use of general anesthesia, patients often experience high levels of preoperative anxiety [3]. This anxiety is a physiological and psychological response to the anticipation of surgery, fear of pain, and loss of control associated with anesthesia [3].

High levels of preoperative anxiety trigger the hypothalamic-pituitary-adrenal (HPA) axis and the sympathetic nervous system, leading to the release of stress hormones such as cortisol and catecholamines [4]. Clinically, this manifests as elevated blood pressure, tachycardia, and tachypnea [5]. These physiological changes can complicate the induction of anesthesia, increase the requirement for anesthetic drugs, and negatively impact wound healing and immune function postsurgery [6,7].

Current management of preoperative anxiety often relies on pharmacological interventions, such as benzodiazepines, which may have side effects like drowsiness or respiratory depression [8]. Consequently, there is growing interest in nonpharmacological alternatives. Virtual reality (VR) is an immersive technology using head-mounted displays, such as the Oculus system, to provide a visual and auditory experience that distracts the patient and reduces anxiety by redirecting attention away from the surgical environment [9]. Over the last decade, numerous studies have evaluated immersive VR as a tool for reducing anxiety, pain perception, and distress in various medical and surgical procedures [9,10]. However, within the field of oral surgery—specifically for complex procedures under general anesthesia—there is a need for comprehensive research that combines subjective psychometric scales with objective biochemical stress markers [10]. Most existing dental VR literature focuses on pediatric populations or minor procedures, leaving a gap in evidence regarding its efficacy for adult patients undergoing oral surgery under general anesthesia [10].

This study aims to determine the effectiveness of VR in reducing preoperative anxiety by analyzing changes in the Amsterdam Preoperative Anxiety and Information Scale (APAIS) scores, vital signs, and specific stress biomarkers—salivary alpha-amylase (sAA) and salivary cortisol [10,11].

## Methods

### Study Design and Setting

This study uses a quantitative experimental design with a randomized pretest and posttest control group structure. The research will be conducted at the Dental and Oral Hospital (RSGM) of Universitas Padjadjaran, Bandung, Indonesia. The protocol is designed in accordance with the Consolidated Standards of Reporting Trials (CONSORT) guidelines for nonpharmacological interventions.

### Participants

Participants will be recruited using purposive sampling based on specific eligibility criteria. Inclusion criteria comprise patients aged 17‐40 years who are scheduled for odontectomy of at least two impacted third molars under general anesthesia. Eligible patients must be in good systemic health (American Society of Anesthesiologists, ASA physical status I or II) and have no prior history of surgery involving general anesthesia. To control for confounding factors affecting stress biomarkers, patients will be excluded if they have a history of endocrine disorders, chronic stress conditions, sleep disorders, or are currently taking medications that alter the HPA axis or autonomic response, such as anxiolytics, antidepressants, corticosteroids, or beta-blockers. Patients with visual or hearing impairments that prevent the use of VR will also be excluded. While patients with severe diagnosed psychiatric disorders are excluded to minimize profound psychopathological confounding, patients with general dental anxiety or phobia remain eligible to ensure the clinical generalizability of the findings.

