### Intervention

To ensure a standardized immersive experience and minimize confounding variables, all study procedures—including the intervention and saliva collection—are scheduled to occur between 08:00 AM and 10:00 AM on the day before surgery, specifically to control for the circadian rhythm of salivary cortisol. Participants are randomly assigned to either the intervention or the control group. In the Intervention group, participants use a head-mounted display (Oculus Quest 2) to view a 10-minute 360-degree immersive video. This content, which has been previously piloted to ensure its clarity and tolerability, systematically simulates the patient’s journey from entering the operating room to the induction of anesthesia, aiming to provide psychological desensitization to the surgical environment. In contrast, the Control group receives 10 minutes of standard verbal education regarding the surgical procedure. This session is supported by a flip chart featuring standard images of the preparation room, operating theater, and recovery room, ensuring the information provided is consistent with the visual content of the VR intervention while lacking the immersive component.

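### The only headset-related exclusion is impaired sight or hearing, so patients prone to seizures, vertigo or severe motion sickness may be enrolled and assigned to the VR session

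*Protocol article*

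**What the plan says.** The Participants section of the protocol article sets out its criteria explicitly. One of them concerns the ability to use the device: "Patients with visual or hearing impairments that prevent the use of VR will also be excluded".

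The other criteria that might bear on the point are:

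- General health: "Eligible patients must be in good systemic health (American Society of Anesthesiologists, ASA physical status I or II".
- Medical history: "patients will be excluded if they have a history of endocrine disorders, chronic stress conditions, sleep disorders".
- Medication acting on the HPA axis or the autonomic response, with examples: "such as anxiolytics, antidepressants, corticosteroids, or beta-blockers".
- Psychiatric history: "patients with severe diagnosed psychiatric disorders are excluded to minimize profound psychopathological confounding".

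The Intervention section gives the two exposures. In the VR arm, "participants use a head-mounted display (Oculus Quest 2) to view a 10-minute 360-degree immersive video". In the other arm, "the Control group receives 10 minutes of standard verbal education regarding the surgical procedure", supported by a flip chart and without a headset. The same section says that the video was tried out beforehand for clarity and for how well it is tolerated; no results are given. Under Outcomes and Data Collection, measurements are taken at baseline, directly after the session and 15 minutes after it.

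**The concern.** The protocol accepts that some patients are unsuitable for VR and excludes them, but it defines unsuitability only by whether the patient can see and hear the video. Whether the patient can tolerate it is left open. Two things are at stake.

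The first is safety. A patient with a foreseeable susceptibility to immersive video could be given the headset on the day before general anaesthesia, when a history question would have identified the risk. The article presents VR as a low-risk option: its abstract concludes that, if effective, "VR could serve as a non-invasive, safe alternative to pharmacological premedication".

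The second is the meaning of the outcomes. Heart rate, blood pressure, respiratory rate, salivary cortisol and alpha-amylase are all read as signs of anxiety. Nausea or dizziness from the headset could move them for another reason, and in one arm only. The protocol already excludes several conditions to protect the biomarkers from extraneous influences, so leaving this source open sits poorly with its own aim.

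**Working it through.** The point concerns eligibility, and the article states no figure on it that could be reproduced. The check is to set each criterion against the three kinds of susceptibility.

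| Criterion (Participants) | Purpose | Does it keep out seizures, vestibular disorder or vertigo, or severe motion sickness? |
|---|---|---|
| Sight or hearing too poor for VR | Ability to follow the video | No. All three can occur with normal sight and hearing |
| ASA I or II | General fitness | Not by its wording. A well-controlled condition can fall within class II |
| Endocrine, chronic stress and sleep disorders | Stated: confounding of stress biomarkers | No |
| HPA-axis or autonomic medication | Same | Not reliably. The list is open-ended but defined by drug effect, and many susceptible people take no such drug |
| Severe psychiatric disorder | Stated: psychopathological confounding | No |

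So a patient with any of the three passes the list as written.

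**Who is exposed.** Only the VR arm wears the headset, and the outcomes are read within minutes of its use.

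**What randomisation does.** Allocation is 1:1 and concealed, so susceptible patients are expected equally in both arms. A reaction to the headset is then part of the effect of being assigned to VR in the population enrolled. If it raises the readings, it offsets some of any anxiolytic effect. The comparison of the arms as randomised stays valid; what suffers is its interpretation as a comparison of anxiety.

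**Illustration under assumptions.** The only input from the documents is 16 patients per arm (Sample Size). The prevalence *p*, the number reacting *k* and the shift *s* are assumed.

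Chance of at least one susceptible patient in the VR arm = 1 − (1 − *p*)^16:

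- *p* = 1%: 1 − 0.851 = 0.149, or 15%
- *p* = 5%: 1 − 0.440 = 0.560, or 56%
- *p* = 10%: 1 − 0.185 = 0.815, or about 81%
- *p* = 20%: 1 − 0.028 = 0.972, or 97%

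Shift of the VR-arm mean = (*k*/16) × *s*. With *s* = 1 SD:

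- *k* = 1: 0.0625 SD
- *k* = 2: 0.125 SD
- *k* = 4: 0.25 SD

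With *s* = 0.5 SD each value halves. The article supplies nothing to choose among these rows.

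**The case against.** The strongest reply is that this is a condensed article: a device check may stand in the full protocol, which is not shown. That would carry the point if the article were silent on suitability for VR. It is not silent: it gives a VR-specific exclusion and draws it narrowly. A fuller check may exist, and if so the sponsor need only say so.

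A second reply is that the article nowhere links 360-degree video to seizures, vertigo or motion sickness. This stands as a limit: that susceptible people may react is an assumption here, and no rate can be attached to it. The article does, however, treat tolerance of the content as something that needed testing.

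Third, there is mitigation. Participants are aged 17 to 40 and ASA I or II, the session is short, the video was piloted, and vital signs follow a rest of at least 5 to 10 minutes. All of this lowers the concern, but none of it determines which patients are admitted. Fourth, enrolling broadly and recording VR symptoms is a defensible alternative that keeps the result more general. It would help interpretation but would not avoid the exposure.

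A reader might also infer more than the text supports:

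- *That one-sided symptoms bias the comparison despite randomisation.* They do not, because they belong to the effect of assignment.
- *That patients who remove the headset are lost from one arm, with a loss of power.* Nothing says they would go unmeasured, and no number of such patients can be derived.
- *That susceptible patients will be randomised.* The text permits it but does not show that it happens.
- *That the abstract's conclusion bears on eligibility.* It is conditional on effectiveness and says nothing about who may enter.

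**Conclusion.** The point holds as a gap in a stated criterion. Followed as written, the list admits patients with known susceptibility to immersive video, who may then be assigned to the headset. The consequences are an avoidable safety exposure and, in the VR arm only, possible dilution of the measured effect and a less clear reading of vital signs and salivary markers as anxiety.

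The conclusion rests on the criteria in the article being complete as regards VR suitability, and on the premise that susceptible patients may react to such a session. The size cannot be derived from the document; the illustrative figures show only that, with 16 patients in the VR arm, meeting at least one susceptible patient is unlikely or nearly certain depending on the prevalence assumed. No claim of selection bias or of a loss of power is made, and the sample size does not change on this account. It is a cheap improvement worth making before recruitment.

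**What to change.** In Participants, extend the VR-suitability exclusion to known susceptibility to immersive video: a history of seizures, of vestibular disorder or vertigo, or of severe motion sickness. The investigators should confirm the final list. Put the history questions to every candidate, whichever arm they may enter, and settle the answers before the envelope is opened, so that eligibility cannot depend on allocation. If the full protocol already contains such a check, a sentence in the article saying so is enough.

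The cost is one sentence and a few screening questions. The Results section describes the study as still in preparation, so the change can precede recruitment; as ethics approval is already in place, it would presumably be submitted as an amendment. The downside is that a few patients become ineligible and the result does not extend to them.

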### Randomization and Blinding

Eligible participants will be randomly allocated (1:1 ratio) into either the Intervention (VR) or Control group. To ensure proper allocation concealment, a computer-generated randomization sequence will be created by an independent researcher not involved in clinical care or data collection. The allocation sequence will be concealed using sequentially numbered, opaque, sealed envelopes, which will only be opened after the patient has consented to participate. Due to the nature of the VR intervention, blinding of patients and the administering clinician is not possible. However, the study will use an assessor-blinded approach; laboratory personnel analyzing the salivary biomarkers, and statisticians conducting the data analysis will be strictly blinded to group assignments.

### Intervention

To ensure a standardized immersive experience and minimize confounding variables, all study procedures—including the intervention and saliva collection—are scheduled to occur between 08:00 AM and 10:00 AM on the day before surgery, specifically to control for the circadian rhythm of salivary cortisol. Participants are randomly assigned to either the intervention or the control group. In the Intervention group, participants use a head-mounted display (Oculus Quest 2) to view a 10-minute 360-degree immersive video. This content, which has been previously piloted to ensure its clarity and tolerability, systematically simulates the patient’s journey from entering the operating room to the induction of anesthesia, aiming to provide psychological desensitization to the surgical environment. In contrast, the Control group receives 10 minutes of standard verbal education regarding the surgical procedure. This session is supported by a flip chart featuring standard images of the preparation room, operating theater, and recovery room, ensuring the information provided is consistent with the visual content of the VR intervention while lacking the immersive component.

### Outcomes and Data Collection

Data collection occurs at three standardized time points: Baseline (immediately before the VR or verbal education intervention), Post-test 1 (immediately after the intervention), and Post-test 2 (15 minutes after the intervention). The subjective anxiety assessment uses the APAIS, comprising 6 items scored on a 5-point Likert scale, with total scores ranging from 6 to 30, categorized from “Not Anxious” to “Panic.” Objective physiological assessments include blood pressure (systolic/diastolic), heart rate, and respiratory rate, which will be measured after the patient has rested for at least 5‐10 minutes.

For objective biochemical assessments, unstimulated saliva samples (4‐5 mL) will be collected via the spitting method at the three designated time points. To ensure optimal long-term preservation of the stress biomarkers prior to enzyme-linked immunosorbent assay (ELISA) analysis, samples will be initially frozen at −10 °C and subsequently transferred to a −80 °C freezer. Salivary Alpha-Amylase (sAA) will be analyzed to measure sympathetic nervous system activity, while Salivary Cortisol will be measured to assess HPA axis activity.

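### The anxiety outcome is the full six-item APAIS total, so a change in information need can be read as a change in anxiety

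*Protocol article*

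**What the plan says.** The Objective paragraph of the abstract gives the instrument its full name, "Amsterdam Preoperative Anxiety and Information Scale, APAIS", and the Introduction repeats it. In Outcomes and Data Collection the article says "The subjective anxiety assessment uses the APAIS, comprising 6 items scored on a" 5-point scale, "with total scores ranging from 6 to 30, categorized from" not anxious to panic. The total is thus graded in bands of anxiety. No anxiety subscore or information subscore is mentioned.

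The Intervention section describes two 10-minute sessions. The VR video follows the patient's "journey from entering the operating room to the induction of anesthesia". For the comparator, "the Control group receives 10 minutes of standard verbal education regarding the surgical procedure", supported by a flip chart with pictures of the preparation room, the operating theater and the recovery room. The same section says that the control information is meant to agree with what the video shows, without the immersion.

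The Statistical Analysis section tests time, group and time-by-group effects. The Methods paragraph of the abstract also lists paired tests.

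**The concern.** The score is read purely as anxiety, yet its name says that part of it concerns information. Both arms supply information between the baseline and post-test measurements, so the sessions act directly on that part. A patient who is just as anxious but has fewer open questions can score lower, and the plan would record this as anxiety relief.

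The APAIS is the only subjective measure listed under Outcomes and Data Collection, and the Discussion predicts lower subjective anxiety on it with VR. The biomarkers and vital signs are untouched by this problem, but they cannot separate the two components within the questionnaire score.

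**Working it through.** **Inputs.** From Outcomes and Data Collection: 6 items, each scored 1 to 5, total 6 to 30. From Sample Size: 16 per group. Not in the documents, and assumed below: the number of information items, k = 1 to 3, and a standard deviation of the total of 4 to 6 points.

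**Reproducing the plan's figure.** Minimum = 6 × 1 = 6; maximum = 6 × 5 = 30. This matches the stated range exactly. Any subset of the items gives a narrower range, so the stated total must include all six items, information items among them.

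**Share of the total.** Range of the total = 30 − 6 = 24 points. Each item contributes 5 − 1 = 4 points.

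| Information items, k (assumed) | Points of range, 4k | Share, 4k/24 | Range of the anxiety items alone |
|---|---|---|---|
| 1 | 4 | 17% | 5 to 25 |
| 2 | 8 | 33% | 4 to 20 |
| 3 | 12 | 50% | 3 to 15 |

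**Effect on within-group change.** Suppose anxiety does not change and each information item falls by 1 point in both arms. The total falls by k points in each arm. The between-arm difference is 0, but the time effect and the paired tests show a fall of k points (1 to 3) that is not anxiety.

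**Effect on the group comparison.** This needs unequal effects on information need. The Intervention section reads as follows:

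- Intended match: the control information is to be consistent with the video, and both sessions last 10 minutes.
- Content: the video runs from operating room entry to induction. The flip chart also shows the preparation room and the recovery room, which lie outside that span.
- Delivery: a recorded immersive video against verbal education.

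Equal effects are therefore intended but not assured, and the direction of any difference cannot be read from the text.

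**Illustration of size.** With no anxiety effect and a between-arm difference δ arising from information items alone, SE = SD × √(2/16), and the chance of P<.05 is Φ(δ/SE − 1.96) + Φ(−δ/SE − 1.96). For SD = 4 and δ = 2: SE = 1.41, δ/SE = 1.41, and the chance is 29%.

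| δ (points) | SD = 4 | SD = 5 | SD = 6 |
|---|---|---|---|
| 0 | 5% | 5% | 5% |
| 1 | 11% | 9% | 8% |
| 2 | 29% | 21% | 16% |
| 3 | 56% | 40% | 29% |

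The first row is the case of equal information effects: the between-arm error rate stays at its nominal 5%. The other rows show what unequal effects would do; they are not a forecast that such effects will occur.

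**The case against.** The strongest reply is that the design already deals with information imbalance. The control session has the same length and is meant to carry information consistent with the video, and the trial's hypothesis concerns VR against verbal education, not change over time. If information need falls equally in both arms, the between-arm comparison is not biased. This stands as far as it goes, and it limits the point: bias between arms is conditional. It does not remove the point, because the described contents are not identical and because the time effect and paired tests are planned and would be affected even under a perfect match.

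A second reply is that the documents do not list the items, so a specific split cannot be asserted. This stands. A reader might infer a definite 4-and-2 split and a definite anxiety range; neither is in the documents, and the ranges above are conditional on k.

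A third reply is that an article may leave scoring detail to a fuller document. Here, however, the article does state a scoring rule: it uses the six-item total and bands it as anxiety. The point concerns that stated rule, not a missing detail.

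A reader might also infer that the trial will give a biased answer about VR, or one that favours VR. The documents support neither. They give no evidence that the arms will differ in their effect on information need, and a difference could run either way.

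**Conclusion.** The point holds in a limited form. The subjective anxiety score contains information content by the scale's own name, and both arms act on that content between measurements. Within-group change, the time effect and the paired tests can therefore show reduced anxiety when only information need has fallen. The group comparison can be biased if VR and verbal education meet information need unequally, which the incomplete match leaves possible but does not show.

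The direction and size of any bias are unknown. On the assumption of 1 to 3 information items, 17% to 50% of the score range is at issue. The error rates above rest further on an assumed standard deviation of 4 to 6 and an assumed arm difference of 1 to 3 points. The salivary markers and vital signs are not affected. This is a worthwhile correction to a stated scoring rule, not a flaw that invalidates the trial.

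**What to change.** In Outcomes and Data Collection, define the subjective anxiety outcome as the sum of the instrument's anxiety items only, naming those items. Report the information items as a separate outcome, so that a reader can see whether the arms differ on anxiety, information need or both. Keep the 6 to 30 total as a supportive summary. Do not apply the anxiety bands to the mixed total: restate them for the anxiety-item score if that can be justified, or drop them.

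The cost is small. The same six items are asked at the same three times, and the Results section places the study in its preparation phase. The anxiety score becomes shorter and may be slightly less reliable. The article gives no standard deviation or target difference, so the effect of the shorter score on power cannot be calculated from it.
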